### Screening survey

#### Eligibility questions

To expeditiously exclude individuals not qualified to participate in this trial, five screening questions will be asked. Participant who respond affirmatively to any of the following questions will be excluded: (1) Do you plan to relocate from this area within the next 5 years? (2) Have you undergone previous intraocular ophthalmic surgery? (3) Have you ever experienced serious eye trauma? (4) Have you been previously treated for glaucoma? (5) Do you have a severe, life-threatening disease, such as end-stage cardiac, renal, or pulmonary disease, or terminal cancer?

#### Informed consent

Ophthalmologists will elucidate the procedures and purpose of this study to potential participants. Should participants or their relatives raise any questions, the physicians will provide detail answers. Informed consent will be obtained from participants only after they have demonstrated a comprehensive understanding of the study.

#### Questionnaire

We will condense the information potentially associated with the onset of PACG into a more concise questionnaire. The questionnaire will include the following components: (1) Personal history, covering education level, employment status (retired or not), daily exercise duration, smoking and alcohol consumption history, family history of glaucoma, light exposure environment (self-reported indoor and outdoor time), and self-assessed personality traits; (2) Detailed ocular history, including ocular surgeries, laser treatment history, and history of ocular trauma; and (3) General medical history, including hypertension, diabetes, coronary heart disease and relevant conditions.

### Ophthalmologic examinations

All participants will undergo a comprehensive ocular examination, including presenting visual acuity (PVA), best-corrected visual acuity (BCVA), and IOP measurement with GAT (Haag-Streit, Koniz, Switzerland). IOP will be measured three times, and the average value recorded. Additional examinations will include undilated slit-lamp biomicroscopy and stereoscopic evaluation of the optic disc using a 90-diopter lens (Volk Optical, Inc., Mentor, OH). PVA and BCVA will be converted to logarithm of the minimal angle of resolution (LogMAR) scores from Snellen acuity. In a safe manner, lens grading will be assessed using a modified version of the Lens Opacity Classification System III (LOCS III) grading system. This assessment will take place subsequent to pupil dilation. We have included the evaluation of IOP and anterior chamber morphology before and after pupil dilation in our study protocol. Limbal anterior chamber depth (LACD) will be evaluated according to the modified van Herick system as a percentage of the adjacent corneal thickness. Patients with LACD ≤25% of peripheral temporal corneal thickness will be referred to gonioscopy. Gonioscopy will be performed in a dimly lit room [illumination less than 10 lux, measured with a luminance meter (Model ST-92, Beijing Teachers University Photoelectricity Instrument Factory, Beijing, China)] by a glaucoma specialist using a Zeiss-style four-mirror gonioscopy lens (Model G-4, Volk Optical, Inc., Mentor, OH) at 16× magnification, both with and without indentation. Five measurements of axial length (AL) will be taken using the IOLMaster 700 (Carl Zeiss Meditec, Inc., Dublin, CA) with a signal-to-noise ratio of more than 100, and the mean value will be used for analysis. Ocular biometry obtained from IOLMaster will include central cornea thickness, anterior chamber depth (ACD), lens thickness (LT), AL, flat keratometry (flat K), steep keratometry (steep K), and white-to-white (WTW) distance. AS-OCT (RTVue 100-2, Optovue, Fremont, California) will be employed to assess anterior segment structures and parameters such as corneal thickness, ACD, angle width, and iris curvature, in a non-contact, and high-resolution manner.

Optical coherence tomography (Spectralis HRA + OCT, Heidelberg Engineering GmbH, Heidelberg, Germany) will be employed to assess retinal nerve fiber layer (RNFL) defects. The visual field (VF) will be evaluated using the Swedish Interactive Threshold Algorithm (SITA) program 24-2 on a Humphrey Field Analyzer (Carl Zeiss Meditec, Inc., Dublin, CA) to identify characteristic glaucomatous VF defect. A characteristic glaucomatous defect is defined as a visual field abnormality consistent with the pattern of optic nerve damage caused by glaucoma (3).

UBM (Aviso, Quantel Medical, Inc., Bozeman, MT) measurements will be conducted using a 50-MHz transducer by well-trained operators blind to the clinical data. All patients will undergo UBM imaging in a supine position under room light [illumination 120 lux, measured with a luminance meter (Model ST-92, Beijing Teachers University Photoelectricity Instrument Factory, Beijing, China)]. After topical anesthesia with oxybuprocaine eye drops, an eyecup containing normal saline will be carefully mounted on the globe. The UBM transducer will be moved perpendicularly over the ocular structures without exerting pressure on the globe or touching the cornea. Measurements will be taken from both eyes in the superior, inferior, temporal, and nasal quadrants, as well as nasal-temporal scans centered on the pupil to obtain a full view of the anterior segment. During dynamic scanning, if the VZ appears on the monitor, the image will be stored. The strand attaching to the posterior VZ insertion zone and posterior lens equator, referred to as PVZ INS-LE, will also be categorized as VZ. All images will be acquired under consistent room lighting condition. Only images with a clear view of the scleral spur, angle, ciliary body, iris, and anterior surface of the lens will be included in the analysis.

### Follow-up visits

In the absence of special circumstances, such as and acute angle-closure attack, patients will visit the glaucoma clinic every 12 months as part of the BAPS. Follow-up examinations will include: BCVA, IOP, undilated slit-lamp biomicroscopy, gonioscopy, UBM, Spectralis HRA + OCT, and VF testing (if suspecting of glaucomatous damage).

### Study endpoint and termination of follow-up (censored data)

The study endpoint will be reached if the participant meets any of the following criteria: (1) An episode of acute PAC; (2) Any PAS; (3) IOP > 21 mmHg; (4) Any patchy TM pigmentation; and (5) Glaucomatous visual field defect, RNFL defects, or glaucomatous abnormality of optic nerve. Participants meeting at least one of the five criteria will be classified in the progression group. For patients experiencing an acute angle-closure attack, the time of progression will be recorded accurately. If chronic progression (PAS or glaucomatous abnormality of optic nerve) is detected during routine follow-up, the progression time will be recorded based on the follow-up time.

The following conditions will be considered reasons for termination of follow-up and will be defined as censored data: (1) Inability to continue follow-up for various reasons, such as severe systemic diseases or relocation; (2) Development of new severe ocular diseases requiring treatment, such as vision-threatened cataract, retinal detachment, or age-related macular degeneration; (3) Missing 3 out of 6 monthly follow-up visits; and (4) Requesting withdrawal of informed consent.

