**Methods/design:**

The BAPS is a clinic-based, multicenter, noninterventional trial conducted on a sample of urban Chinese adults. Consecutive eligible patients who meet PACS diagnostic criteria will be recruited from eight participating centers, with the trial commencing on August 4, 2022. The target sample size is set at 825 subjects, with follow up planned for a minimum period of 5 years. Baseline examination will include presenting visual acuity, best corrected visual acuity, intraocular pressure (IOP), undilated slit-lamp biomicroscopy, stereoscopic evaluation of the optic disc, visual field test, optical coherence tomography evaluation of retinal nerve fiber layer, ultrasound biomicroscopy and IOLMaster. Questionnaires will also be used to collect detailed personal history. Patients are scheduled to visit the glaucoma clinic every 12 months and may visit the emergency room in case of acute attack of angle closure. Study endpoints include acute PAC episodes, elevated IOP, peripheral anterior synechiae, glaucomatous visual field defect, or glaucomatous abnormality of optic nerve.

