## Introduction

Although the global prevalence of primary angle-closure glaucoma (PACG) is less than half that of primary open-angle glaucoma, it poses a significantly higher risk of causing severe bilateral blindness, with rate three times greater than primary open-angle glaucoma (1). PACG is a leading cause of irreversible blindness worldwide (2), characterized by the closure of the anterior chamber angle. Primary angle-closure suspect (PACS), the earliest stage of primary angle-closure diseases (PACD), is defined as 6 or more clock hours of appositional contact between the peripheral iris and posterior trabecular meshwork on gonioscopy. Progression from PACS to primary angle-closure (PAC) involves elevated intraocular pressure (IOP) or the presence of peripheral anterior synechiae (PAS), while PACG involves these features along with glaucomatous optic neuropathy or glaucomatous visual field defects (3). It is estimated that by 2040, the number of PACG cases worldwide is projected to reach 32 million, with a significant proportion occurring in Asia (4, 5). Therefore, a better understanding of the natural history of PACD may play an important role in preventing devastating visual impairment.

Previous studies have reported the prevalence of PAC and PACG ranging from 1 to 11.3% (6–9). However, longitudinal data on the incidence and progression of earlier stages of angle closure that precede PAC/PACG are scarce, particularly in Asian population (10–14). For instance, a Danish study demonstrated that the rate of progression from the condition of shallow anterior chamber to PACG was 16% over 10 years (15). In Asia, PACS progression rates to PAC or PACG range from 5.3 to 25.5% (10–14). Identified risk factors for progression include bilateral PACS (10), smaller angle width (11), shorter angle open distance, flatter iris curvature, and older age (12).

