## Materials and methods

### Study design and principal aims

The BAPS is a clinic-based, multicenter, noninterventional trial conducted on a sample of urban Chinese adults. This study has been approved by the ethics committee of Peking University People’s Hospital and will adhere to the tenets of the Declaration of Helsinki. The protocol is prospectively registered at www.cilinicaltrials.gov (registration number NCT05563623). Institutional Review Board/Ethics Committee approval has been obtained.

The comprehensive study protocol is summarized in Table 1, providing an overview of the study design and key steps.

**Table 1 tab1:** Comprehensive study protocol for the Beijing angle closure progression study.

Step	Description	Details
Study design	Clinic-based multicenter noninterventional trial	Conducted on a sample of urban Chinese adults
Ethics approval	Approved by the Ethics Committee	Peking University People’s Hospital, follows the Declaration of Helsinki
Registration	Protocol registered	www.clinicaltrials.gov (NCT05563623)
Participant recruitment	Recruitment centers	8 participating centers
Inclusion criteria	Criteria for eligibility	6 or more clock hours of angle circumference with no PAS and normal IOP Aged 40–75 years Provide informed consent
Exclusion criteria	Criteria for exclusion	Evidence of PAC or PACG Previous intraocular surgery or laser treatment Severe health problems
Baseline examination	Comprehensive initial examination	Visual acuity IOP measurement Slit-lamp biomicroscopy Gonioscopy OCT UBM
Follow-up visits	Regular follow-up schedule	Every 12 months, including examinations for IOP, visual acuity, gonioscopy, UBM, OCT, and visual field testing
Study endpoints	Criteria for study endpoint	Acute PAC episode Elevated IOP (>21 mmHg) Presence of PAS Glaucomatous visual field defects
Data management	Handling and storing data	Non-image data in BAPS Database Image/original data stored securely Privacy of participants protected
Statistical analysis	Data analysis methods	SPSS 22.0 for analysis Significance level: 0.05 Independent *t*-test, Mann–Whitney U test, Pearson chi-square test, logistic regression analysis, Cox regression analysis

IOP, intraocular pressure; PAS, peripheral anterior synechiae; PAC, primary angle-closure; PACG, primary angle-closure glaucoma; OCT, optical coherence tomography; UBM, ultrasound biomicroscopy; BAPS, Beijing angle closure progression study.

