### Clinical data collection

All subjects will be screened through a preliminary survey to verify their eligibility for recruitment in this trial. A comprehensive baseline examination will be conducted for every enrolled subject. Patients will be monitored for 5 years. All examinations involving subjective judgment and manipulation, such as Goldmann applanation (GAT), UBM, and gonioscopy, will be performed by experienced examiners.

For the analysis, we will enroll only one eye per subject to avoid correlation issues between eyes of the same individual. The selection of which eye to include will be randomized to ensure that there is no selection bias.

Inclusion criteria are as follows: (1) Static gonioscopy identifying six or more clock hours of angle circumference in which the posterior (usually pigmented) trabecular meshwork is not visible in both eyes with no PAS, and normal IOP, optic nerve, and visual field; (2) Patients aged between 40 and 75 years; and (3) Patients capable of providing informed consent.

Exclusion criteria are as follows: (1) Any evidence of PAC, characterized by a narrow angle as defined above, but with PAS and/or IOP > 21 mmHg, or PACG, indicated by a visual field defect or glaucomatous optic neuropathy; (2) Previous intraocular surgery or laser treatment, including cataract surgery, laser trabeculoplasty, trabeculectomy, laser peripheral iridectomy, and laser iridoplasty; (3) Signs of prior acute attack, such as glaucomatous fleck, keratic precipitates, or iris atrophy; (4) Anterior segment structural abnormalities, such as iris or ciliary body tumor; (5) Severe health problems that preclude follow-up, such as end-stage heart disease, kidney disease, lung disease, or terminal cancer; (6) Severe eye diseases requiring treatment, such as cataract, macular disease, and retinal detachment; and (7) Patients who plan to move from the area within the next 5 years.

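### Patchy trabecular meshwork (TM) pigmentation alone counts as progression, yet it is outside the article's own definition of PAC/PACG and is neither excluded by name at entry nor limited to new onset

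*Protocol article*

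**What the plan says.** The section on study endpoint and termination of follow-up gives five criteria, the fourth being "4) Any patchy TM pigmentation". It then states: "Participants meeting at least one of the five criteria will be classified in the progression group". Pigmentation is therefore sufficient on its own.

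The disease definitions elsewhere are narrower. The Introduction says: "Progression from PACS to primary angle-closure (PAC) involves elevated intraocular pressure (IOP) or the presence of peripheral anterior synechiae (PAS"; it reserves PACG for eyes with these features plus glaucomatous optic neuropathy or field defects. Exclusion criterion 1 uses the same boundary at entry: "Any evidence of PAC, characterized by a narrow angle as defined above, but with PAS and/or IOP > 21 mmHg".

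Three other places say what counts as an endpoint or outcome:
- Abstract: "Study endpoints include acute PAC episodes, elevated IOP, peripheral anterior synechiae, glaucomatous visual field defect, or glaucomatous abnormality of optic nerve".
- Table 1: "Acute PAC episode Elevated IOP (>21 mmHg) Presence of PAS Glaucomatous visual field defects".
- Statistical analysis plan section: the primary outcome is the progression rate, explained as the rate of acute PAC (IOP above 21 mmHg) and the share of eyes in which PAS appear.

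None of the three mentions pigmentation. At entry, the inclusion criteria ask for no PAS and for normal IOP, optic nerve and visual field. Exclusion criterion 3 covers "Signs of prior acute attack, such as glaucomatous fleck, keratic precipitates, or iris atrophy". Pigmentation is not named in either list.

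**The concern.** Both principal aims depend on who is placed in the progression group. The 5-year incidence counts those participants, and the baseline comparisons and the logistic and Cox models use the same split. An endpoint sign should either be absent at entry or be counted only when it is new. Otherwise prevalent and incident findings are mixed.

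The fourth criterion meets neither condition. Its wording asks for any pigmentation, not for a change. An eye enrolled with the sign could meet the endpoint at its first annual gonioscopy and enter the Cox model as an early event.

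Even pigmentation that is new would not, by itself, be PAC or PACG as the article defines them. The reported figure would then describe something other than the stated aim.

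**Working it through.** **1. The statements side by side**

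| Place in the protocol article | What defines progression or disease | Pigmentation? |
|---|---|---|
| Endpoint section | Five criteria, any one sufficient | Yes, criterion 4 |
| Introduction | PAC: raised IOP or PAS; PACG: plus nerve or field damage | No |
| Exclusion criterion 1 | PAC: PAS and/or IOP > 21 mmHg; PACG: field defect or neuropathy | No |
| Abstract | Acute PAC, IOP, PAS, field, nerve | No |
| Table 1 | Acute PAC, IOP, PAS, field | No |
| Statistical analysis section | Acute PAC (IOP > 21 mmHg), PAS | No |

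**2. Endpoint criteria against entry criteria**

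Criteria 1, 2, 3 and 5 each have a counterpart at entry: signs of a prior attack, PAS, IOP > 21 mmHg, and nerve or field damage. (RNFL defects are covered only indirectly, by the normal optic nerve requirement.) Criterion 4 is the only one with no counterpart.

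**3. The plan's own figures**

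The article assumes a 20% incidence, 700 evaluable participants and 15% attrition. 700 / (1 − 0.15) = 823.5, so 824 against the stated 825, which is reproduced to rounding. The sample size does not depend on this point. The planned event count is 0.20 × 700 = 140.

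**4. Illustration of the possible effect**

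Let p be the true incidence and f the share of non-progressing eyes scored on pigmentation alone. The article gives no value for f, so 2%, 5% and 10% are assumptions.

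- Reported incidence = p + (1 − p)f
- False events = 700 × (1 − p)f

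With p = 0.20:

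| f | Reported incidence | False events | Share of all events |
|---|---|---|---|
| 2% | 0.20 + 0.80 × 0.02 = 21.6% | 11.2 | 11.2/151.2 = 7% |
| 5% | 0.20 + 0.80 × 0.05 = 24.0% | 28 | 28/168 = 17% |
| 10% | 0.20 + 0.80 × 0.10 = 28.0% | 56 | 56/196 = 29% |

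For scale, the 95% half-width around 20% with 700 participants is 1.96 × √(0.20 × 0.80 / 700) = 3.0 percentage points. The shift of 0.80 × f exceeds that once f passes about 3.7% (0.0296 / 0.80).

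At 5.3%, the lowest Asian rate the article cites, true events are 0.053 × 700 = 37.1. With f = 10%, false events are 0.947 × 0.10 × 700 = 66.3, or 64% of 103.4.

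**5. Illustration for the risk-factor models**

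Assume half the participants are exposed, the true risk ratio is 2.0, and pigmentation-only scoring is unrelated to exposure. At an overall 20%, the risks are 0.1333 and 0.2667. Replacing each risk r by r + (1 − r)f gives:

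- f = 2%: 0.2813 / 0.1507 = 1.87
- f = 5%: 0.3033 / 0.1767 = 1.72
- f = 10%: 0.3400 / 0.2200 = 1.55

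**The case against.** **Omission from the other lists is weak evidence taken singly.** The abstract says only that endpoints include certain items. Table 1 also leaves out optic nerve abnormality and RNFL defects. The primary outcome in the analysis section leaves out field and nerve damage too. This stands, but the two disease definitions do not rely on abbreviated lists, and both leave pigmentation out.

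**The entry criteria may already exclude the sign.** The prior-attack list is introduced by examples, and exclusion 1 refers to any evidence of PAC, so an examiner could exclude a pigmented angle. Words such as progression and developing also suggest change. This is fair, but nothing requires that reading.

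**A reader might infer that the incidence will be inflated.** The documents do not show this. It needs eligible eyes that carry the sign, unchanged pigmentation being scored, and the endpoint section governing the analysis. If the primary outcome in the analysis section governs instead, the headline rate is unaffected. Nor is dilution of associations certain: if pigmentation is related to angle anatomy, the bias could take another form. Lost comparability with the Indian study used for planning cannot be checked either, because the article does not give that study's PAC criteria.

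**A reader might also infer that the IOP criterion scores eyes that have not progressed.** The documents do not support that. IOP above 21 mmHg is within the article's own definition of PAC, and the recorded value is the mean of three measurements. A repeat-visit rule may sit in the full protocol, which a condensed article need not reproduce. The article does say "We have included the evaluation of IOP and anterior chamber morphology before and after pupil dilation in our study protocol", but its follow-up examination list contains no dilation, so nothing shows a post-dilation reading being scored as an endpoint. Any false-positive rate would rest wholly on IOP means and standard deviations that the article does not give.

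**Conclusion.** The endpoint section is wrong as written on pigmentation. It makes sufficient for progression a sign that the article's own definitions of PAC and PACG do not contain, that no other endpoint statement mentions, and that is neither named as an entry exclusion nor restricted to new onset. It should be corrected because it decides which participants are events for both principal aims.

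The size is unknown. The rise from 20% to between 21.6% and 28.0% holds only for assumed values of f from 2% to 10%, and only where the endpoint section governs classification. The shrinkage of a risk ratio of 2.0 to between 1.87 and 1.55 also assumes 50% exposure and pigmentation-only scoring unrelated to exposure. What the text establishes is an unreconciled contradiction and a route by which an unchanged eye can be counted as an event. The verdict does not extend to the IOP criterion.

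**What to change.** - Remove patchy TM pigmentation from the primary PAC/PACG composite.
- Report it as a secondary sign, counted only as new onset in eyes recorded free of it at baseline. Baseline gonioscopy is already performed on every enrolled participant, since eligibility rests on it; the added work is recording the sign.
- Make the abstract, Introduction, Table 1, entry criteria, endpoint section and primary outcome state the same set of events.

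If the investigators prefer to keep pigmentation in the composite, excluding it by name at entry or requiring new onset would remove the prevalent-sign problem. The mismatch with the PAC/PACG definition would still have to be resolved.

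The cost is mainly wording. The small downside is fewer counted events, and so slightly less information for the risk-factor models. Reporting incidence with and without IOP-only events is at most an optional sensitivity analysis.

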**Figure 1 fig1:**
[figure not shown]
Outline of the workflow for screening and enrollment in the BAPS.

The principal aim of this trial is to explore the 5-year incidence of PACS progressing to PAC or PACG and to determine the risk factors for disease progression.

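### PACG and progression are defined differently in four places, and endpoint criterion 5 counts glaucomatous damage alone, which the Introduction classes as neither PAC nor PACG

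*Protocol article*

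**What the plan says.** The stated aim, under Study design and principal aims, is PAC or PACG: "The principal aim of this trial is to explore the 5-year incidence of PACS progressing to PAC or PACG".

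Four parts of the protocol article bear on what that means.

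- **Introduction.** For PAC: "Progression from PACS to primary angle-closure (PAC) involves elevated intraocular pressure (IOP) or the presence of peripheral anterior synechiae (PAS"). For PACG: "while PACG involves these features along with glaucomatous optic neuropathy or glaucomatous visual field defects (3"). Damage is therefore added to raised IOP or PAS and does not replace them.
- **Clinical data collection, exclusion criterion 1.** After describing PAC as a narrow angle with PAS and/or IOP above 21 mmHg, it continues: "or PACG, indicated by a visual field defect or glaucomatous optic neuropathy". IOP and PAS are not restated as conditions for PACG.
- **Study endpoint and termination of follow-up.** "The study endpoint will be reached if the participant meets any of the following criteria". Criterion 1 is an acute episode. Criteria 2 to 4 are "2) Any PAS; (3) IOP > 21 mmHg; (4) Any patchy TM pigmentation". The last is "5) Glaucomatous visual field defect, RNFL defects, or glaucomatous abnormality of optic nerve". The rule that joins them is "Participants meeting at least one of the five criteria will be classified in the progression group".
- **Statistical analysis plan.** The primary outcome is the progression rate, explained as the rate of acute PAC (IOP above 21 mmHg) and the proportion of eyes developing PAS. No field, RNFL or disc component is named. The same section compares the progression and non-progression groups and fits logistic and Cox models for progression to PAC or PACG.

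**The concern.** An incidence study depends on its case definition. If the Introduction governs, criterion 5 can put an eye in the progression group that has not progressed to PAC or PACG as recorded. If the exclusion wording governs, the same eye is a PACG case. If the Statistical analysis plan section governs, that eye is outside the primary rate but still inside the progression group used for the risk-factor comparisons. The reported 5-year incidence and the cases in the models could then rest on different definitions within one report.

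The RNFL component is the loosest part. An RNFL defect is named in neither description of PACG. Under Follow-up visits, OCT is done at every annual visit, while field testing is done when damage is suspected. The component with the least definition is therefore looked for in everyone, every year.

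**Working it through.** **Step 1. Which eyes does criterion 5 add?** Take every combination of PAS, IOP above 21 mmHg and glaucomatous damage, with criteria 1 and 4 absent.

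| PAS | IOP > 21 | Damage | PAC/PACG by Introduction | PAC/PACG if exclusion wording accepts damage alone | Counted by criteria 2–3 | Counted with criterion 5 |
|---|---|---|---|---|---|---|
| no | no | no | no | no | no | no |
| no | no | yes | **no** | **yes** | **no** | **yes** |
| no | yes | no | yes | yes | yes | yes |
| no | yes | yes | yes | yes | yes | yes |
| yes | no | no | yes | yes | yes | yes |
| yes | no | yes | yes | yes | yes | yes |
| yes | yes | no | yes | yes | yes | yes |
| yes | yes | yes | yes | yes | yes | yes |

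Criterion 5 changes the classification in one row of eight: damage with neither PAS nor IOP above 21 mmHg. That row is also the only one on which the two descriptions of PACG disagree. Every eye that meets the Introduction's PACG description already meets criterion 2 or 3.

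**Step 2. Base for an illustration.** Sample size estimation gives 700 participants with complete follow-up and 20% progression. The 700 agrees with the planned enrolment: 700 / (1 − 0.15) = 823.5, against 825 stated. Expected progressors are 0.20 × 700 = 140, leaving 560.

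**Step 3. How many eyes might be affected?** The document gives no rate of damage without PAS or raised IOP. Assume an annual rate r, constant over 5 years, applying to the 560 not otherwise progressing.

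- 5-year risk: x = 1 − (1 − r)^5
- Damage-only eyes: 560 × x
- Share of counted events: 560x / (140 + 560x)
- Counted incidence: (140 + 560x) / 700

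| Assumed r per year | x | Damage-only eyes | Share of counted events | Counted incidence |
|---|---|---|---|---|
| 0.1% | 0.0050 | 2.8 | 2.0% | 20.4% |
| 0.2% | 0.0100 | 5.6 | 3.8% | 20.8% |
| 0.5% | 0.0248 | 13.9 | 9.0% | 22.0% |

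The range is therefore about 3 to 14 eyes and 2% to 9% of counted events.

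**The case against.** The strongest reply is that the Introduction is background prose, while the exclusion criterion is the Methods wording actually used to classify participants. Every enrolled eye has a narrow angle. If damage in such an eye indicates PACG, criterion 5 matches the study's own entry rule. This stands in part: the exclusion wording can be read that way. It can also be read as PAC plus damage, and it does not say which. Breadth is also harmless in a baseline exclusion but not in an outcome.

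A second reply is that visits are 12 months apart, so raised IOP or PAS can be missed. A stand-alone damage criterion would catch such eyes. In other eyes damage may be seen first and PAS or raised IOP later, and criterion 5 then only moves the event time earlier. Both points stand and are the reason for keeping these eyes visible in the report.

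A third reply is that the Statistical analysis plan section leaves damage out of the primary outcome, so the primary rate may not be affected. This stands if that section governs. The progression-group comparisons would still be affected.

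A reader might infer three stronger things, none of which the document supports.

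- **Criterion 5 captures only eyes that are not PACG.** This holds against the Introduction alone, and only for findings as recorded.
- **Up to 31% of events could be of this kind.** That figure pairs the highest assumed rate with 5.3%, the low end of the Asian range in the Introduction: 0.947 × 0.0248 / (0.053 + 0.947 × 0.0248) = 0.31. The Introduction gives no follow-up period for that range, so 5.3% cannot be taken as a 5-year risk.
- **These eyes would dilute the UBM associations.** This needs a clinical premise about what predicts damage without angle-closure features, and the document does not supply one.

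**Conclusion.** The inconsistency is real and should be resolved before analysis. The Introduction, the exclusion criteria, the endpoint section and the Statistical analysis plan section do not share one definition of PACG or of progression. Under the Introduction's definition, criterion 5 adds only eyes that are neither PAC nor PACG as recorded.

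The size is unknown. The 2% to 9% of counted events rests on assumed annual rates of 0.1% to 0.5%, 20% progression by the other criteria, and 700 participants followed for the full 5 years. It shows that the effect on overall incidence is probably modest if the true rates lie in that range. It is not an estimate, and it does not show that the primary rate is inflated, because that depends on which section governs.

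**What to change.** 1. Reconcile the four sections to one definition of PACG and one of progression to PAC or PACG. Use it for both the primary rate and the progression group. State whether an RNFL defect without field or disc change counts, and whether criterion 4 is retained.
2. Classify eyes that meet criterion 5, with no PAS, IOP above 21 mmHg, acute episode or other retained criterion at the same or an earlier visit, as a separate category: glaucomatous change without recorded angle-closure features.
3. Report the 5-year incidence and the logistic and Cox models with and without this category. State in advance how these eyes are handled over time in the models that leave them out, since some may show PAS or raised IOP later.

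The cost is a change of wording and one extra analysis. IOP, gonioscopy and OCT are already scheduled at every visit, so no new data are needed. The downside is that a few true PACG eyes with a missed IOP rise or missed PAS leave the main count. The analysis that adds the category back recovers them.
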